### Analysis

The primary objective of the evaluation is to assess the impact of AGEP on adolescents’ intermediate empowerment and longer-term outcomes using the above-noted hypothesis as test criteria. Important as well, analysis will be conducted to understand the underlying processes by which change occurred in the key areas of interest. As a first approach for assessing the impact of AGEP on empowerment and longer-term outcomes, an intent-to-treat analysis (ITT) will be conducted using the original randomised assignment to study arm as the primary indicator of impact. The average treatment effect of the programme on the adolescents in clusters randomised to AGEP relative to girls in clusters randomised to the control will be empirically assessed. The analysis will estimate models that are both unadjusted and adjusted for baseline covariates; both approaches accounting for strata and intraclass correlations within clusters. To accommodate for any baseline differences between AGEP and control clusters that may exist in the outcomes, a difference-in-differences (DID) calculation will be made for each indicator. The mid-term assessment after Round 3 focused on the immediate and mediating indicators as primary outcomes, while in the final assessment after Round 5 the mediating and longer-term outcomes will be the empirical focus.

As girls were invited to participate in AGEP, many choose not to do so, intermittently missed the weekly sessions or left the programme before the programme was completed. Therefore a secondary analysis will be conducted that uses a measure of participation intensity as the indicator of impact rather than the study’s random assignment. It is important to recognize the statistical estimation problems that arise from self-selection into AGEP, and the degree of participation in it, with the characteristics of girls predicting both their uptake of and exposure to the programme and key outcomes and behaviours of interest. A two-stage instrumental variables estimation approach will be used in which the first stage will predict programme participation, using the exogenous randomised assignment as the key instrumental variable, observed baseline covariates will also be included. The second stage will then use the predicted participation intensity from the first stage along with baseline covariates to test the relevant hypotheses. Appropriate tests, including F-tests on excluded instruments, the Wald F-statistic, and the Hansen statistic for over-identification will quantitatively assess the credibility of the selected instrumental variable.

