## Background

This paper reviews the design and methods of a multi-arm, randomized cluster evaluation of the Adolescent Girls Empowerment Programme (AGEP) in Zambia. The programme was designed as a multi-sectoral intervention targeted to vulnerable, rural and urban adolescent girls ages 10–19. Embedded in the design of the programme was a rigorous, randomized evaluation that recruited a cohort of eligible adolescent girls invited to participate in the programme and girls residing in control areas. The evaluation sample was interviewed at baseline in late 2013 and early 2014 and is being tracked annually through 2017, with mid-term results collected in 2015 immediately after the end of the intervention and endline results in 2017, two years post programme termination [1].

Adolescent girls in less developed countries face a variety of risks and challenges in achieving positive and successful transitions to adulthood [2]. In Zambia, a significant proportion of girls enter marriage and/or begin childbearing early, even prior to the expected age of school leaving. As indicated by the 2013–2014 Zambia Demographic and Health Survey (DHS), nearly one in three girls aged 20–24 had married by age 18, with a similar percentage having begun childbearing [1]. The prevalence in rural areas is nearly double that of urban areas for both early marriage (39% versus 22%) and early childbearing (42% versus 21%) [3]. Not surprisingly, given rates of early marriage and childbearing, the risk of school leaving for girls during the school age years is high, with 18% of primary school age girls and 59% of secondary age girls not currently attending school [1]. The Zambia DHS also indicates that girls in Zambia begin sexual activity early, have low rates of condom use and have risk behaviours that increase their chances of acquiring sexually transmitted infections (STIs), including HIV. For instance, the median age of sexual debut is 17.7 years, approximately 1 year prior to marriage, and the prevalence of sexual initiation among 15–19 year olds is 27%. Further, of those who are currently engaging in premarital sexual activity, only 36% reported using a condom at last sex. The low rate of consistent condom use implies exposure to STIs, with 4% of adolescents 15–19 reporting having an STI or symptoms of a sexually transmitted disease and 5% having acquired HIV. The prevalence of HIV more than doubles by the time girls reach the ages of 20–24 years [1].

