### Research population and sample sizes

Participants for the research study were randomly selected among all invited AGEP participants who were never married at baseline, stratified by site and age group. For comparability, selection of the control girls followed a parallel process for identifying and selecting vulnerable girls, specifically a ranking of girls by their vulnerability score and randomly selecting girls below a set threshold, with the threshold determined by the total number of girls needed for recruitment into the programme at each site. As the ultimate objective of the funder and the programme was to improve the well-being of adolescent girls, the longer-term outcomes in Table 4 served as the focal indicators for the sample size calculations. As limited evidence was available for a sample size determination based on known effect sizes, minimally detectable effects were estimated using Optimal Design Plus Software Version 3.0 for a multi-site randomized trial to determine the most efficient sample size (number of clusters and respondents per cluster) given the budget available for fieldwork [25]. Sample sizes were estimated for the evaluation after four years, with conservative estimates of attrition, 20% for the younger cohort and 35% for the older cohort. The samples were stratified by the younger and older cohorts (10–14 and 15–19) and urban and rural. The age stratification was necessary as there was no age mixing of groups in the weekly girls groups and certain aspects of the curricula were adjusted for age-appropriateness by cohort.

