Biological markers were collected from adolescents aged 15 and older at baseline (Round 1), after Round 3 (at the end of AGEP), and Round 5 (at the end of the evaluation). HIV status was determined via capillary blood draws obtained from finger pricks. HIV tests were conducted by trained and certified voluntary counselling and testing (VCT) staff. In accordance with Ministry of Health guidelines, we conducted serial testing using Determine™ and Uni-Gold™ [27]. Both tests have a very high sensitivity (100%) and specificity (>99%) in controlled clinic evaluations, including a controlled laboratory setting in rural Kenya [28]. The respondent was provided the test results. Post-test counseling was guided by National Guidelines for Testing and Counselling [29].

The HSV-2 biological specimens were collected via finger prick. A sample of whole blood was collected and stored in microtainers and laboratory tested. To conduct the laboratory test, serum was derived from the whole blood and the Kalon ELISA assay used, for which the sensitivity and specificity have been found to be high (92% and 98%) respectively in African populations when compared to Western Blot [30]. Indeterminate results were not retested since their prevalence was so low as to make it impractical. After specimen collection all participants were provided information about HSV-2 detection, symptoms, safe sex practices and treatment options. Respondents were provided vouchers with identification numbers to receive their test results at AGEP participating health centers. A validation of the HSV-2 laboratory testing procedures was conducted prior to testing of specimens for the main study to assure the quality of laboratory testing protocols.

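### Difference-in-differences for every indicator cannot be computed for younger-cohort HIV and HSV-2, adds nothing for marriage, and is a weaker way to handle baseline differences in one-way outcomes than regression on the Round 1 value

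*Protocol article*

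**What the plan says.** The Analysis section of the protocol article leads with randomised arm: "an intent-to-treat analysis (ITT) will be conducted using the original randomised assignment to study arm as the primary indicator of impact". It then states: "The analysis will estimate models that are both unadjusted and adjusted for baseline covariates", with allowance for strata and clustering. A further step is then added: "a difference-in-differences (DID) calculation will be made for each indicator". No indicator is excepted. The purpose given for this step is "To accommodate for any baseline differences between AGEP and control clusters that may exist in the outcomes".

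Three other places bear on that step.

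- Research population and sample sizes: "Participants for the research study were randomly selected among all invited AGEP participants who were never married at baseline". Controls were chosen by a parallel process, and the same section names never-married girls as the baseline target. The age cohorts are 10–14 and 15–19.
- Research instruments: "Biological markers were collected from adolescents aged 15 and older at baseline (Round 1"), with later collections after Round 3 and at Round 5.
- Tables 4 and 5: ever married, births, grade 7 and grade 9 completion, HIV and HSV-2 are longer-term indicators. Table 5 gives younger-cohort figures for HIV (6%, ±4 pp) and HSV-2 (21%, ±8 pp).

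**The concern.** A DID needs a baseline value that exists, that can vary, and whose gap between arms would carry over one-for-one to endline if the programme did nothing. Several longer-term indicators fail at least one of these conditions.

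Younger-cohort biomarkers have no Round 1 value. Ever married has no baseline variation. Births, grade completion, HIV and HSV-2 cannot be reversed, so an arm that starts with more cases has fewer girls left who can change. Part of a chance baseline gap then closes without any programme effect. DID subtracts the whole gap, which flatters the arm that started worse.

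At stake is how far the step does the job the article gives it, for outcomes that are a focus of the final assessment after Round 5, and how much precision is lost compared with using the same baseline data as a covariate.

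**Working it through.** **Design inputs reproduced.** 40 clusters × 20 girls = 800 per arm; × 4 = 3200; + 400 external controls = 3600; baseline 4800 + 1600 + 800 = 7200. All agree with the article. With 400 girls per arm per age cohort (40 × 10), two-sided alpha 0.05 and power 0.80, the detectable reduction for older births from 70% is 9.4–10.3 pp for an ICC of 0–0.02, against 10 pp in Table 5. The article gives no ICC. None of its figures depends on the DID, so this confirms only the inputs.

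**Can the DID be computed?**

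- Younger HIV and HSV-2: girls aged 10–14 at baseline were under 15 at Round 1. No baseline value exists, so there is no DID. This holds whether the age limit applies at each round or only at baseline. On the second reading the younger cohort is never tested at all.
- Ever married: baseline is 0 in each arm, so DID = (endline difference) − 0 = endline difference.

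**One-way outcomes.** Let p0 be the baseline rate, p1 the endline rate, and h = (p1 − p0)/(1 − p0). The slope of endline on baseline is 1 − h. With a chance imbalance d and no effect:

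- endline comparison is off by (1 − h)d;
- DID is off by (1 − h)d − d = −h×d;
- regression on the baseline value is off by about 0.

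Per-girl variances:

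- endline: p1(1 − p1);
- DID: (p1 − p0)(1 − p1 + p0), which equals the endline variance + (2h − 1)p0(1 − p0);
- baseline-adjusted: p1(1 − p1) − (1 − h)²p0(1 − p0), which equals the DID variance − h²p0(1 − p0).

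So in large samples DID is never more precise than the adjusted model, and it is less precise than the endline comparison only when h exceeds 0.5.

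**Older births**, p1 = 0.70 (Table 5), p0 = 0.20 (assumed):

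- h = 0.50/0.80 = 0.625. With d = 5 pp, DID is off by −3.1 pp and the endline comparison by +1.9 pp.
- Variances: endline 0.21; DID 0.50 × 0.50 = 0.25; adjusted 0.21 − 0.375² × 0.16 = 0.1875. SE ratio of DID to adjusted = √(0.25/0.1875) = 1.155.
- Plausibility of d: the SE of the baseline gap is √(2 × 0.2 × 0.8/400) = 2.8 pp before clustering, and 4.0 pp with 200 per arm in a rural or urban stratum.

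**Range over assumed baseline rates** (the article gives none for this sample):

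| Outcome (Table 5 endline) | Assumed p0 | h | SE, DID/adjusted | SE, DID/endline |
|---|---|---|---|---|
| Births, older (70%) | 10–30% | 0.57–0.67 | 1.10–1.18 | 1.07–1.09 |
| Grade 7, older (60%) | 30–50% | 0.20–0.43 | 1.06–1.11 | 0.61–0.94 |
| HSV-2, older (26%) | 5–15% | 0.13–0.22 | 1.01 | 0.71–0.93 |
| HIV, older (12%) | 2–6% | 0.06–0.10 | 1.00 | 0.73–0.92 |
| Births, younger (16%) | 0–2% | 0.14–0.16 | 1.00 | 0.95–1.00 |

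**Simulation check** (40 v 40 clusters of 10, ICC 0.03 assumed, 3000 runs per setting). For older births with p0 20% and a true effect of −7.50 pp, the DID mean was −7.48, with SDs of 3.77 (DID), 3.31 (adjusted) and 3.52 (endline). With no effect, DID means lay within 0.2 pp of zero in every setting. For older births with no effect, the slope of the estimate on the baseline imbalance was −0.67 for DID, +0.33 for endline and −0.04 for the adjusted model.

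**The case against.** The strongest reply is that randomisation makes DID unbiased, that the lead analysis is intent-to-treat with baseline-adjusted models already planned, and that DID is an added calculation. All of this stands, and it limits the point in four ways.

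- A reader might infer that DID biases the trial's results. The documents and the simulation do not support that. The error is conditional on a chance imbalance and averages out over randomisation. It can also be smaller than the error from ignoring baseline: for older HSV-2 with 10% assumed at baseline, a 5 pp imbalance leaves DID off by −0.9 pp and the endline comparison by +4.1 pp.
- A reader might apply the rule that change scores lose precision whenever the baseline–endline correlation is below 0.5. That rule needs equal variances at both times, which one-way outcomes do not have. Here the condition is h above 0.5, and DID beats the unadjusted endline comparison for older grade 7 and HSV-2.
- The largest precision loss is for older ever had sex (82% in Table 5; SE ratio 1.37–1.39 for 30–50% assumed at baseline). But that indicator is not in Table 4. The Background figure that "the prevalence of sexual initiation among 15–19 year olds is 27" per cent is a national rate, not one for vulnerable never-married girls. It would also be wrong to say that Table 5's detectable effects are worsened, since none rests on DID.
- Deleting DID altogether goes too far. Self-efficacy, knowledge scores and savings can move both ways. Restricting to girls free of the outcome at Round 1 would change the prevalence and ever-type indicators on which Table 5 was sized.

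The redundancy for marriage is harmless. What the reply does not meet is the missing younger-cohort baseline, or the fact that the article names DID, not covariate adjustment, as its remedy for baseline differences in the outcomes.

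**Conclusion.** The point holds in a limited form. As written, the DID rule conflicts with the biomarker schedule for two indicators in one of the two age cohorts; that follows from the text alone. For one-way outcomes it over-corrects a chance imbalance by the onset proportion, and it is no more precise than regression on the baseline value in large samples. The loss is material for older births and moderate for older grade 7, and about nil for HIV, HSV-2 and younger births. The older-births error of −3.1 pp is about three-tenths of the 10 pp detectable effect, but only if a 5 pp imbalance occurs.

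The sizes rest on assumed baseline rates, on onset not depending on arm under no effect, and, in the simulation, on an assumed ICC. This is a worthwhile correction to a stated method, not a threat to the validity of the intent-to-treat comparison.

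**What to change.** Replace the blanket DID sentence with the following:

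- Baseline differences are handled by the adjusted intent-to-treat model: the Round 3 or Round 5 outcome on arm, the Round 1 value of the same outcome where measured, site and age stratum, with allowance for clustering.
- Ever married is compared at endline. So are younger-cohort HIV and HSV-2, provided these girls are tested at Round 5; the biomarker paragraph should say whether its age limit applies at each round or only at baseline.
- DID is kept at most as a sensitivity analysis, for indicators measured at Round 1.

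The cost is a change of wording. The Round 1 data needed are part of the existing collection, and neither the sample nor the indicators change.

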### Randomised cluster design

The AGEP evaluation was designed as a multi-arm randomised cluster trial where clusters within the ten study sites were randomised to receive different combinations (arms) of AGEP. The experimental and control arms of the study are displayed in Table 3, along with their associated components. Clusters assigned to the first intervention arm were assigned only the weekly girls’ group sessions. Clusters in the second intervention arm were assigned the health voucher in addition to the weekly girls’ group sessions, while clusters in the final intervention arm were assigned all components, including the bank account. The multi-arm evaluation provided for a rigorous assessment of the marginal benefit, as well as the incremental cost-effectiveness of each additional component of the intervention. All girls selected for participation in AGEP within a cluster were assigned to the intervention that was randomly selected for that cluster; girls in clusters for the control arm received neither interventions nor placebo exposures.

**Table 3 Tab3:** Randomisation arms of AGEP

Study arm	AGEP components
Intervention arm 1	Weekly girls group mentor-led sessions
Intervention arm 2	Weekly girls group mentor-led sessions + health voucher
Intervention arm 3	Weekly girls group mentor-led sessions + health voucher + bank account
Control	No components of the AGEP intervention

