#### Health voucher

As with the bank account component, the health voucher intervention is hypothesized to directly increase access to health facilities and resources, as well as to increase efficacy and decision-making control over the utilization of health facilities and resources. The effect of the heath voucher component is expected to be distinguishable empirically over and above what is realized through the weekly girls groups alone. In the immediate term, the health voucher is hypothesized to increase the use of sexual and reproductive health services, including the use of modern contraception. Improved sexual and reproductive health, e.g., by obtaining counselling, care and treatment for STIs, is hypothesized to reduce HIV acquisition in the longer-term, while access to contraception is hypothesized to reduce unwanted pregnancy and birth outcomes. In general, it is hypothesized that as specific health issues are prevented or resolved, girls will have more positive assessment of their overall health.

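### The Hansen test named for the instrumental-variable analysis either does not exist or tests whether the arms work equally well per unit of participation, so it cannot vouch for randomised assignment as an instrument

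*Protocol article*

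**What the plan says.** The Analysis section of the protocol article makes intent-to-treat the first approach. It adds a secondary, two-stage instrumental-variable analysis because invited girls may have declined, "intermittently missed the weekly sessions or left the programme before the programme was completed".

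- **Endogenous variable.** The analysis "uses a measure of participation intensity as the indicator of impact" in place of random assignment.
- **Instrument.** The first stage predicts participation, "using the exogenous randomised assignment as the key instrumental variable". The text does not say whether assignment enters as one indicator or as one per arm. No other instrument is named.
- **Second stage.** "The second stage will then use the predicted participation intensity from the first stage along with baseline covariates to test the relevant hypotheses". Baseline covariates are in both stages, so they are not excluded instruments. No voucher or account term appears.
- **Diagnostics.** The list is "F-tests on excluded instruments, the Wald F-statistic" and the Hansen statistic. The aim is that "the Hansen statistic for over-identification will quantitatively assess the credibility of the selected instrumental variable".

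Table 3 (Randomised cluster design) gives three active arms, the fullest being "Weekly girls group mentor-led sessions + health voucher + bank account". The Health voucher hypothesis describes that component's effect as "expected to be distinguishable empirically over and above what is realized through the weekly girls groups alone". The Bank accounts hypothesis likewise expects the account to change savings behaviour beyond what the lessons do.

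**The concern.** F-tests and the Wald F concern instrument strength. The Hansen statistic is the only listed diagnostic that bears on exclusion, the assumption that assignment changes outcomes only through measured participation. A Hansen test needs more excluded instruments than endogenous regressors, and it takes as given that one effect per unit of participation applies to every instrument. The first condition fails with a single assignment indicator. The second conflicts with the trial's own hypotheses once each arm has its own indicator.

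Two things are at stake. The promised check could be missing from the report, or a rejection could be taken as a fault in an instrument that was in fact randomised. Also, a single participation coefficient is meant to test hypotheses that the protocol sets out by component, and it cannot separate groups, voucher and account.

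**Working it through.** The protocol gives no figure for this analysis, so there is none to reproduce. The degrees of freedom and the form of the null are algebra. The sizes rest on assumed inputs.

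**1. Degrees of freedom** = excluded instruments - endogenous regressors.

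- AGEP v control, pooled: 1 - 1 = 0. No test.
- One arm v control, arm by arm: 1 - 1 = 0. No test.
- Three arm indicators, one participation measure: 3 - 1 = 2.

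**2. What the 2-df test tests.** Let *b* be the effect of full group participation, *v* and *a* the direct voucher and account effects, and *p* the mean participation, equal in the active arms and zero in control. The effect per unit of participation (Wald ratio) is

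- arm 1: *b*
- arm 2: *b* + *v*/*p*
- arm 3: *b* + (*v* + *a*)/*p*

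The Hansen null is that these three are equal. With equal participation, that means *v* = 0 and *a* = 0. With unequal participation it is still equality of the three ratios, so effect heterogeneity or a non-linear dose-response can also cause rejection. A direct effect proportional to participation leaves the ratios equal and goes undetected.

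**3. Pooled coefficient, if participation means group attendance.** Assume *p* = 0.5, a groups intent-to-treat effect of -4 pp, and a further -4 pp in arms 2 and 3.

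- Groups alone at full participation: -4/0.5 = -8 pp.
- Pooled: (-4 - 8 - 8)/3 = -6.67 pp; -6.67/0.5 = -13.3 pp, and 13.3/8 = 1.67.
- Add-ons of -2 pp: (-4 - 6 - 6)/3/0.5 = -10.7 pp.
- Add-ons of +2 pp, working against the groups: (-4 - 2 - 2)/3/0.5 = -5.3 pp. The distortion reverses.
- In general the pooled coefficient is *b* + (2*v* + *a*)/(3*p*). With *b* = -0.10 and *v* = *a* = -0.05 it is -0.27, -0.20 and -0.17 at *p* = 0.3, 0.5 and 0.7.

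**4. Simulation of the test.** From the protocol: 40 clusters per arm, 20 girls per cluster, alpha 0.05. Assumed: control prevalence 0.40, intraclass correlation 0.03, *p* = 0.5, *b* = -0.10. Two-stage least squares with a cluster-robust Hansen statistic, 1,000 replicates per row, three arm indicators:

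| *v* | *a* | mean coefficient (true *b* = -0.10) | Hansen rejects |
|---|---|---|---|
| 0 | 0 | -0.101 | 4.7% |
| -0.05 | 0 | -0.168 | 34.8% |
| -0.05 | -0.05 | -0.201 | 82.5% |
| -0.10 | 0 | -0.233 | 89.7% |
| -0.10 | -0.05 | -0.267 | 99.6% |

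Assignment is truly random in every row. In the second row the test misses the add-on path in about 65% of trials while the coefficient is already well away from *b*. With *b* = 0 and *v* = *a* = -0.05 the mean coefficient is -0.097. With one indicator the coefficients are nearly the same and the Hansen statistic is zero, to rounding, in every replicate. Twenty girls per cluster combines both age cohorts; Table 5 plans 10 per cohort, so power within a cohort would be lower.

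**The case against.** The case on the other side has several parts.

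- **Estimand.** The Analysis section speaks of participation in the programme, and the programme includes the add-ons. On the illustration's inputs the full-participation effects by arm are -8, -16 and -16 pp, averaging -13.3 pp, which is what the pooled analysis returns. This stands: the figure is biased only as an effect of attending groups. A reader might infer that the planned estimate is simply 67% too large; the article does not define participation closely enough to support that.
- **Delivery through the groups.** Add-on eligibility followed the location of the girls' group, vouchers went to girls who attended, and account orientation took place in sessions. So exclusion is not shown to be false for every definition of participation, and much of the difference can be seen as different versions of treatment. This stands in part. The Health vouchers section says the voucher remained in use for a year after the groups stopped, which an attendance count cannot capture, and a composite measure would still impose one effect per unit on all components.
- **Pooling is inferred.** The text does not say that the arms are combined, and an arm-by-arm analysis fits it. This stands, and the absorption of add-on effects is conditional for that reason. Arm by arm, however, the Hansen statistic is again undefined.
- **Other instruments.** Calling assignment the key instrument leaves room for others, such as assignment by site. None is named, and such terms would add degrees of freedom without closing the voucher and account paths.
- **Condensed article.** The definition of participation and the list of instruments may be in a fuller document, and their absence here is no fault. The diagnostic, however, is stated, and it fails under each reading that the text supports.

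It is also tempting to say that the test rejects exactly when the add-ons work. It does not: power can be low, and heterogeneity can also trigger it.

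**Conclusion.** The point holds as a defect in a stated diagnostic. The Hansen statistic is undefined with one assignment indicator. With three it tests equality across arms of the effect per unit of participation, which the protocol's component hypotheses expect to fail. Neither result judges the randomised instrument: rejection is ambiguous, and non-rejection does not establish exclusion. This part needs no numerical assumption.

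If arms are pooled and participation means attendance at groups, the coefficient can be read only as an average package effect. The -13.3 v -8 pp contrast shows the possible size; its size and direction depend on the assumed participation and component effects.

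A reader might infer that the trial's main result is compromised. It is not: intent-to-treat by assigned arm does not use this model. Nor is arm 1 v control guaranteed free of exclusion problems. The article expects change to spread to family and community, adds external control clusters because of contamination, and asks about exposure in order to address spillover. The matter is worth correcting, at the level of a secondary analysis.

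**What to change.** - Run the instrumental-variable analysis separately for each arm v control, or in one model with three arm-specific participation variables and three arm indicators (3 - 3 = 0 over-identifying restrictions).
- Interpret only arm 1 v control as the effect of group participation. Label the arm 2 and arm 3 coefficients as package effects.
- Delete the Hansen statistic. Report the first-stage F.
- Argue exclusion on design grounds, and acknowledge that spillover could breach it in any arm, including arm 1.
- State what the participation measure counts and which indicators are the instruments.

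The cost is a change of wording and a different regression, with no new data. The group-participation estimate would use two of the four randomised arms, 80 of 160 clusters as planned, so its intervals would be wider.
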